### Background of the practitioners

The study treatments will be performed by Registered Chinese Medicine Practitioners (RCMPs) in Hong Kong who each have more than 3 years of experience in acupuncture and are trained in administering warm needling acupuncture. The RCMPs in this study should strictly adhere to the study protocol and train to be familiar with administering the study treatments. The practitioners will be asked to maintain the same attitude toward each individual to avoid any psychological influences.

### Treatment procedure

During each treatment session, the treatment group will receive electroacupuncture plus warm needling therapy on the affected heel(s) at one Ashi point [19, 35] and at Shuiquan (KI5, the cleft point of the Kidney Meridian) [36, 37]. The Ashi point is a tender point that is not included in the classic acupuncture points [19, 36]; it is frequently used in treating heel pain with an effect on relieving pain [15, 24, 25]. The literature has shown that combining one or more cleft point in acupuncture treatment for heel pain has a more effective result [38]. The location of the Ashi point used in this study is the anteromedial aspect of the painful heel (or heels) with marked tenderness, and KI5 is determined based on the guidelines presented in the World Health Organization Standard Acupuncture Point Locations in the Western Pacific Region [37]. For individuals with pain in both heels, treatment will be provided bilaterally.

Treatments will be administered using sterile, single-use, disposable acupuncture needles with guide tubes (size, 0.25 mm × 40 mm; Wuxi Jiajian Medical Instrument Co., Ltd, Wuxi, China). During the treatment, the room temperature will be maintained at 25 ± 3 °C, and the individual will lie in the supine position with the affected heel(s) exposed. The skin will first be sterilized before needle insertion. After that, needles will be inserted perpendicularly for all selected acupuncture points to a depth of 20 mm, followed by the stimulation methods of lifting and thrusting combined with twirling and rotating the needles evenly to achieve a dull ache, numbness or heaviness sensation, called *deqi* [39, 40]. All needles will be retained in situ for 30 min. During the retaining period, electrical stimulation and warm needling therapy will be administered simultaneously.

Paired electrodes of the electroacupuncture apparatus (Hwato SDZ-III; Suzhou Medical Appliance Factory, Suzhou, China) will be connected to the needles at the Ashi point and KI5 on the same side of the heel. Electrical stimulation will be delivered with a dense-disperse wave and a frequency of 2 Hz. The intensity of the electric current will be increased to the patient’s maximum tolerance and then slightly reduced to a bearable and comfortable level.

The bottom of a cylinder-shaped moxa stick (Changsha Furong Huai, Changsha, China), which measures 12 mm in diameter and 15 mm in length and weighs 0.7 ± 0.05 g, will be ignited and attached to the needle handle for each acupuncture point. The needle handle will be inserted into the center of the cylinder-shaped moxa stick. The ignited end will be oriented toward the skin and placed 3 cm from the skin surface, which is an appropriate and safe distance for administering moxibustion [41–43]. When the first moxa stick has burned fully, the ashes will be removed, the second stick will be placed, and the same procedure will be followed. In total, two moxa sticks will be applied to each acupuncture point. The burning time for each moxa stick is approximately 10 min. The total moxibustion time for two moxa sticks will be approximately 20 min, an advisable time and within the effective thermal stimulation range for moxibustion [41, 44]. The individual will feel a sense of local warmth without burning pain, and the surrounding skin will become mildly red during the procedure. The needles will be removed after the retention time and at the end of moxibustion.

Precautionary measures should be taken for warm needling therapy. In the process of inserting the ignited moxa stick into the needle handle, the practitioner holds the junction of the needle body with one hand while inserting the moxa stick into the needle at the inserted acupuncture points gently with the other hand to prevent skin burns. After attaching the moxa stick to the needle handle, the practitioner should ensure that the stick is fully fixed into the needle handle to prevent it from falling onto the skin surface. When placing the second moxa stick and removing the needles at the end of the treatment, the practitioner should take note of the temperature of the needles to prevent burns. The practitioner must be aware of the individual’s sensitivity to temperature and pain, and advise the individual not to let the acupuncture points become uncomfortably hot. The individual will be closely monitored during the entire procedure to ensure safety and to guarantee that any accident is handled in a timely manner [45].

### Permitted and prohibited concomitant treatments

During the study period, which includes the follow-up period, individuals will not be allowed to use other pain control interventions in relation to their heel pain, which includes but is not limited to other acupuncture treatments, bone setting, physiotherapy, and medication. Such interventions could influence the study results. The practitioner will advise the participants to avoid other treatments, and this advice will be reinforced by investigators during the entry period and at each evaluation time point. In the event that an individual has utilized other cointerventions for heel pain, such as taking pain-relief medications, this information should be reported to investigators during each evaluation period, and the information will be recorded for analysis. However, general light exercises and self-massage will be allowed for all individuals participating in the study.

### Study termination

The study will be stopped if the principal investigator believes that there is an unacceptable risk of serious adverse events during the study treatments.

### Outcome measurements

In the study, the unit of analysis will be selected on an individual basis, regardless of whether one or both heels were affected [46]. Individuals with pain in one heel or in both heels will be included without discrimination. Outcomes for heel pain and foot function will be assessed in heels with more severe symptoms.

#### Primary outcome measure

The primary outcome measure will be the mean change in the pain intensity of the first step (i.e., first-step pain) between the baseline and after treatment (i.e., week 4). First-step pain is the pain experienced after a long period of not bearing weight, such as upon first stepping out of bed in the morning, and is a common complaint of individuals with plantar heel pain [3, 15], measured with a 100-mm VAS. The VAS for pain is a widely used measurement of pain intensity [47–49]. It is a continuous scale ranging from 0 to 100, where 0 represents “no pain” and 100 represents the “worst imaginable pain”.

#### Secondary outcome measures

Secondary outcome measures include the mean change in the first-step pain VAS score from the baseline to week 2. The same VAS used for the primary outcome measure will be applied again. In addition, the mean change in the Foot Function Index (FFI) subscale scores and total score from the baseline to week 2 and week 4 and the patients’ self-reported level of improvement at week 4 will also be measured as secondary outcomes.

The FFI is a frequently-used self-reporting measure of foot-specific pain and disability; it has good reliability and validity [49–51]. In this study, the Chinese version of the validated FFI [52] will be used. It consists of 23 items divided into three subscales: Pain (nine items), Disability (nine items), and Activity Limitation (five items). Each item will be rated on a VAS, which is a horizontal line without numbers or divisions. The poles are labeled “no pain” and “worst pain imaginable” for the Pain subscale; “no difficulty” and “so difficult unable” for the Disability subscale; and “none of the time” and “all of the time” for the Activity Limitation subscale. Each item score is derived by dividing the attached horizontal line into 10 equal segments and assigning a number ranging from 0 to 9 to each segment. A subscale score is calculated by summing the item scores for the subscale, dividing it by the maximum total possible score for all of the subscale items that the individual indicated as applicable, and then multiplying the value by 100. Any item marked “not applicable” will be excluded from the total possible score. Subscale scores range from 0 to 100. The total foot function score is derived by averaging the three subscale scores together. A higher score indicates greater impairment and a lower level of functioning (i.e., greater disability or loss of function).

The participants’ self-reported level of improvement will be measured on the 15-point Global Rating of Change (GRC) scale [53, 54]. Each number on the 15-point GRC scale represents a different change in health status. The numbers range from − 7 to + 7 as follows: − 7, “a very great deal worse”; − 6, “a great deal worse”; − 5, “a good deal worse”; − 4, “moderately worse”; − 3, “somewhat worse”; − 2, “a little worse”; − 1, “almost the same, hardly any worse at all”; 0, “no change”; + 1, “almost the same, hardly any better at all”; + 2, “a little better”; + 3, “somewhat better”; + 4, “moderately better”; + 5, “a good deal better”; + 6, “a great deal better”; and + 7, “a very great deal better”.

#### Subsidiary observation

For the longer-term evaluation of the effects of electroacupuncture plus warm needling therapy in the treatment group, a subsidiary assessment will be conducted at week 8 for the primary and secondary outcome measures.

#### Adverse events

For safety concerns, all unexpected and unintended responses that are not necessarily related to the study treatments will be recorded with a detailed explanation such as the time of occurrence, duration of symptoms, seriousness of symptoms (mild, moderate, or severe [55]), management measures, time of adverse reaction disappearance, and causality categorization (i.e., “certain”, “probable or likely”, “possible”, “unlikely”, “unclassified”, or “unclassifiable” [56]) at every visit on an adverse event report. Adverse events that are associated with acupuncture and moxibustion include acute pain, bruising, bleeding, burns, blisters, dizziness, anxiety, and infection [55, 57]. Investigators will record and manage all adverse events, regardless of whether it is relevant to the study treatment.

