**Fig. 2 Fig2:**
[figure not shown]
Schedule of enrollment, interventions, and assessments. ^1^Only the treatment group will undergo the week 8 assessment and visits for ± 4 days are allowed. VAS visual analog scale, GRC Global Rating of Change

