### Follow-up visits

The acupuncture and moxibustion used in this study are based on traditional Chinese medicine theory and a review of the literature. A previous study [31] has shown that warm needling acupuncture has a synergistic and more effective analgesic effect than acupuncture without heat or than heat applied to the skin surface. The treatment group will undergo a total of six treatment sessions because previous articles and reviews have shown that six or more acupuncture treatments were significantly associated with positive outcomes [32, 33]. The treatment regimen in this study will involve six treatment sessions of electroacupuncture plus warm needling therapy within a 4-week period on a regular basis (i.e., one treatment session every 3–5 days). The treatments will be provided at no cost to the participants. Assessments and a questionnaire will be administered on the day of the treatment session at week 2 (i.e., after the third treatment), at week 4 (i.e., after the sixth treatment), and at week 8 (for longer-term treatment effect evaluation).

No intervention will be provided for the waitlist control group during the study period. The participants will be informed that they are required to visit the Chinese Medicine Centre at week 2 and week 4 for study assessments. Considering that heel pain is an annoying condition and may affect a patient’s daily life, it may not be appropriate to start treatment after a longer waiting period. Therefore, participants will be scheduled to receive six acupuncture treatments for heel pain for free at their own discretion after the week 4 study assessments. No week 8 study assessments will be arranged for the control group because that would not provide a valid comparison with the treatment group.

To promote subject retention and complete follow-up, the study investigators will make every reasonable effort to follow the participants for the entire study period and provide timely reminders to the patients regarding their treatment or assessment schedule. A designated telephone line will be provided to all study participants to report adverse events during office hours.

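### Adverse events are recorded at every visit, but the treated arm has six visits by week 4 plus week 8 and controls have two, so any side-by-side display of event rates is open to ascertainment bias against the treatment

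*Protocol article*

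**What the plan says.** The Adverse events section has events recorded "at every visit on an adverse event report", with time of occurrence, duration, severity, management and a causality category. The scope is deliberately wide: "Investigators will record and manage all adverse events, regardless of whether it is relevant to the study treatment".

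The visits differ by arm. Under Follow-up visits, the treated arm has "six treatment sessions of electroacupuncture plus warm needling therapy within a 4-week period", one every 3–5 days. Its week 2 and week 4 assessments take place on treatment days, after the third and sixth sessions. Controls are told that "they are required to visit the Chinese Medicine Centre at week 2 and week 4 for study assessments". The Fig. 2 caption adds: "Only the treatment group will undergo the week 8 assessment".

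Follow-up visits also gives every participant a telephone line for reporting adverse events in office hours. It explains that controls are not assessed at week 8 because the comparison with the treated arm would not be valid. Safety is an aim alongside efficacy in the Abstract and in Study objective and hypothesis. The Statistical methods and analysis section names no adverse event analysis.

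**The concern.** The rule is the same sentence for both arms, but it acts on different visit schedules. The number of times a patient is asked, and the time over which they are asked, therefore depend on allocation.

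Because unrelated events are collected in an untreated arm, a reader of the results will naturally use the control events as the background rate. Several reactions that the protocol lists, such as dizziness, anxiety and acute pain, also occur without needling. If controls are asked less often and for less time, the background is understated and ordinary complaints can pass for effects of treatment. The trial is open-label, so causality ratings are not a reliable way to separate the two.

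Part of this cannot be repaired at analysis. Time of occurrence is recorded, so the data can be cut at week 4. Control events that were never elicited, or were forgotten between widely spaced contacts, cannot be recovered.

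**Working it through.** **Inputs from the protocol article.** Treated visits to week 4: 6, because the assessments fall on session days and add none. Treated visit after week 4: 1 (week 8). Control visits: 2, and none after week 4. Group size: 40 (Sample size calculation). The protocol states no adverse event rate, so there is no figure of its own to reproduce on this point.

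**Reading taken.** A treatment session counts as a visit. Data management supports this, since it distinguishes data from visits from data from outcome assessments.

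**Assumptions, not in the documents.** The background hazard λ is the same in both arms at 0.02, 0.05 or 0.10 events per person-week, and the treatment causes no events. Sessions are evenly spaced, 4/6 = 0.67 week apart (about 4.7 days, within the stated 3–5), which puts session 3 at week 2 and session 6 at week 4.

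**Step 1: contacts and window.** By week 4: 6/2 = 3 to 1. Overall: 7/2 = 3.5 to 1. Observation: 8/4 = 2 to 1.

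**Step 2: full schedule pooled, complete recall.** Expected events = 40 × λ × weeks. Proportion with at least one event = 1 − exp(−λ × weeks).

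| λ | Events, treated (8 wk) | Events, control (4 wk) | At least one event, treated | At least one event, control |
|---|---|---|---|---|
| 0.02 | 6.4 | 3.2 | 14.8% | 7.7% |
| 0.05 | 16 | 8 | 33.0% | 18.1% |
| 0.10 | 32 | 16 | 55.1% | 33.0% |

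The ratio of expected counts is 2.0 at every λ and needs no assumption of forgetting.

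**Step 3: baseline to week 4 only.** With complete recall both arms have 40 × λ × 4 expected events, a ratio of 1.0. Now suppose that an event is reported at the next visit with a probability that falls exponentially with the time since it occurred, with time constant τ. An interval of length g then yields λτ(1 − exp(−g/τ)) reported events per person. The treated arm has six intervals of 0.67 week and controls have two of 2 weeks, so λ cancels:

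ratio = 6(1 − exp(−0.67/τ)) / 2(1 − exp(−2/τ))

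| τ (weeks) | Events per 40 at λ = 0.05, treated | Control | Ratio to week 4 | Ratio, full schedule |
|---|---|---|---|---|
| complete recall | 8.0 | 8.0 | 1.00 | 2.00 |
| 4 | 7.4 | 6.3 | 1.17 | 1.97 |
| 2 | 6.8 | 5.1 | 1.35 | 2.03 |
| 1 | 5.8 | 3.5 | 1.69 | 2.26 |

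The event columns cover baseline to week 4. The last column adds the treated arm's 4-week interval to week 8.

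**Step 4: the fix under the same model.** If both arms are asked at weeks 2 and 4 about the whole interval, both have two 2-week intervals. The ratio is then 1.0 at any τ (8.0 against 8.0 at λ = 0.05 with complete recall).

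**The case against.** The strongest reply is that the protocol does not plan the comparison that would be harmed. It asks for case-level description, names no between-arm test of adverse events, and may leave tabulation to an analysis plan that is not shown. Nor does it propose setting treated weeks 0–8 against control weeks 0–4; it calls week 8 a subsidiary observation in the treatment group. Time of occurrence and causality are recorded, so a week 4 cut is available. The telephone line serves both arms and does not depend on visits. Closer enquiry where needles and burning moxa are applied is ordinary safety practice, and any bias runs against the treatment.

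Most of this stands and limits the point. It does not remove it. The telephone line waits for the patient to call, so it reduces the imbalance without equalising enquiry. A week 4 cut settles the window but not the 6 against 2 enquiries inside it. A plain side-by-side table misleads in the same way as a test.

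Two stronger readings are not supported:

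- A reader might infer that week 4 rates must differ widely even under no effect. For example, if each enquiry had the same 10% chance of eliciting an event, 1 − 0.9^6 = 47% of treated patients and 1 − 0.9^2 = 19% of controls would report one. That lets an enquiry covering 3–5 days yield as much as one covering about 14, so controls report background events at one third of the treated rate by assumption. Nothing in the documents supports equal yield.
- A reader might infer that late reactions to session 6 are lost. They can still be recorded at the week 8 visit or by telephone. They only fall outside a window shared with controls.

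**Conclusion.** The point holds as a weakness in how adverse events are collected. It is not a flaw in any stated analysis. Contacts of 6 against 2 by week 4 and 7 against 2 overall follow directly from the text, given that sessions count as visits.

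The doubling over the full schedule rests only on an equal, constant background hazard, and it arises only if the two windows are pooled. The week 4 ratio of about 1.2 to 1.7 rests on an assumed recall decay with a time constant of 4 weeks to 1 week; with complete recall it is 1.0. These are expected values, and observed rates could agree or differ by chance. The telephone line would bring the week 4 ratio nearer to 1.0 by an amount that the documents do not allow one to estimate.

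The direction is against the treatment. The primary outcome and the sample size are not affected. It is worth correcting because safety is a stated aim and the remedy is cheap.

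**What to change.** Amend the Adverse events section as follows:

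1. At the existing week 2 and week 4 contacts, ask both arms the same fixed question, covering the whole interval since the last assessment, and keep recording time of occurrence.
2. Base any between-arm comparison or side-by-side display only on those reports, within baseline to week 4.
3. Report events elicited at the other treatment sessions, and all events after week 4 including those with onset after session 6, separately as treated-arm descriptive data.

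This takes one paragraph, one item on the existing form and a second adverse event table. It adds no visits and leaves safety recording at treatment sessions as it is. It equalises the enquiry; it does not remove differences in reporting that come from patients knowing their allocation.

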#### Dropouts and withdrawals

All dropouts and attrition during the course of the study will be monitored, and the respective reasons for withdrawal will be recorded.

### Data management

Data will be collected after acquiring the signed consent forms from the participants. All data from the visits will be recorded in the medical records, and all data from the outcome assessments will be collected using paper-based questionnaires. The collected data will be anonymized and recorded on case report forms. All data will be confidential, and access to the data will be limited to delegated research personnel. All study-related physical data and information will be stored securely in a double-locked cabinet in a dedicated office at the study site that is secured by a code-operated lock and is only accessible by delegated research personnel. All electronic datasets will be password protected. The participants’ study information will not be released outside the study without obtaining the written permission of the participant. After the trial, all documents will be preserved in the secure research archives at the study site for 7 years and will be deleted after the completion of the storage period.

### Statistical analysis

#### Sample size calculation

The sample size calculation will be based on the primary outcome and evaluated with the OpenEpi statistical program [58]. The sample size estimate is based on a two-arm normal design. A two-sided test with an α level of 0.05 and 80% power detects a minimally important difference of 19 mm with a standard deviation of 28 mm (first-step pain as measured by the VAS) [54]. With an assumed attrition rate of 10%, each group will require 40 individuals, which implies a total sample size of 80 individuals for the entire trial.

#### Statistical methods and analysis

The statistical analysis will be conducted based on the intention-to-treat principle. Continuous variables will be summarized using the means and standard deviations or the means and 95% confidence intervals. Categorical variables will be summarized using counts and percentages.

The measurement data will first be tested using a normality test. For the descriptive analysis, data will be evaluated for normality and log-transformed when necessary. Two-sample *t* tests or the Wilcoxon rank-sum tests for continuous data and Pearson chi-squared tests or Fisher’s exact tests for categorical data will be conducted, depending on whether the data are normally distributed or skewed.

For the primary outcome, the paired *t* test or Wilcoxon signed-rank test will be used to perform a within-group comparison on the mean change between scores assessed before and after treatment. The two-sample *t* test or Wilcoxon rank-sum test will be used for comparisons between groups. The mean differences in other secondary outcome measures will be analyzed by following the same methodology used in the primary outcome measurement. In addition, longitudinal mixed-effects model repeated-measures tests will also be conducted to analyze the mean change in outcome measurements from the baseline to the end of the trial between the two study groups.

Analyses of data in this study will be performed using SPSS (IBM Corp, Armonk, NY, USA) and/or Stata software (StataCorp LLC, College Station, TX, USA). Multiple imputation techniques will be used to manage missing values. All tests will be two-sided, and *P* < 0.05 will be considered statistically significant.

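### A normality test decides whether the primary comparison is of means or of ranks, and no result is named as decisive

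*Protocol article*

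**What the plan says.** All references are to the Protocol article.

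- **Endpoint.** Primary outcome measure: "The primary outcome measure will be the mean change in the pain intensity of the first step", from baseline to week 4, on a 100-mm VAS.
- **Sizing.** Sample size calculation: "The sample size estimate is based on a two-arm normal design", with a 19 mm minimally important difference, SD 28 mm, two-sided α 0.05, 80% power, 10% attrition and 40 per group.
- **Gate.** Statistical methods and analysis: "The measurement data will first be tested using a normality test". The choice between parametric and rank tests is made "depending on whether the data are normally distributed or skewed". Neither the normality test nor its threshold is named.
- **Primary comparison.** Same section, in the paragraph on the primary outcome: "The two-sample *t* test or Wilcoxon rank-sum test will be used for comparisons between groups".
- **Further model.** Same paragraph: "In addition, longitudinal mixed-effects model repeated-measures tests will also be conducted", on the between-group difference in mean change. It is not labelled primary, secondary or sensitivity.
- **Missing data.** Same section: "Multiple imputation techniques will be used to manage missing values".

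Every test is read at two-sided P < 0.05.

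**The concern.** The t test and the rank-sum test answer different questions. The first compares mean changes. The second compares rank order and, unless a pure location shift is assumed, says nothing direct about a mean difference in millimetres. If the gate sends the trial to the rank-sum test, the designated comparison no longer addresses the quantity that defines the endpoint, and its result cannot be set directly against the 19 mm used for sizing.

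Multiple imputation adds a practical problem. Each completed dataset can give its own normality verdict, so the gate may not return one answer. If it points to the rank-sum test, that test does not directly supply the estimate and standard error that the usual pooling rules combine.

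The mixed model then gives another result for the same contrast. If the results differ, the text does not say which one is the trial's answer. In an open-label trial with a self-reported outcome, an analysis settled only after the data are seen is hard to defend.

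**Working it through.** **1. Reproduce the stated sample size.** Inputs from Sample size calculation: difference 19 mm, SD 28 mm, two-sided α 0.05, power 0.80, attrition 10%.

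n per group = 2 × (1.960 + 0.842)² × 28² / 19² = 2 × 7.849 × 784 / 361 = 34.1, so 35. The t-based solution is 35.08, so 36.

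Allowing for attrition: 35 / 0.9 = 38.9, so 39; 36 / 0.9 = 40. The stated 40 per group (80 in total) reproduces. With 36 completers per arm, power is about 0.82. The trial is therefore sized for a comparison of means.

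**2. Simulate the stated rule.** The document gives no distribution for VAS change, so these inputs are assumptions:
- 36 completers per arm, 8,000 trials per row.
- Baseline VAS between 50 and 100 mm.
- Week-4 VAS = 0.6 × baseline + 22 + error − shift in the treated arm, clipped to 0–100.
- Errors either normal (SD 26) or right-skewed exponential (SD 24).
- Gate: Shapiro-Wilk at 0.05 in each arm; rejection in either arm leads to the rank-sum test.
- A baseline-adjusted linear model stands in for the mixed model.

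Proportion of trials with P < 0.05:

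| Errors | Shift (mm) | t | Rank-sum | Gate-selected | Adjusted | Any of three |
|---|---|---|---|---|---|---|
| Normal | 0 | 0.048 | 0.047 | 0.050 | 0.048 | 0.063 |
| Normal | 12 | 0.463 | 0.443 | 0.463 | 0.470 | 0.514 |
| Normal | 19 | 0.846 | 0.827 | 0.845 | 0.855 | 0.877 |
| Skewed | 0 | 0.052 | 0.049 | 0.051 | 0.052 | 0.076 |
| Skewed | 12 | 0.647 | 0.789 | 0.787 | 0.670 | 0.805 |
| Skewed | 19 | 0.949 | 0.984 | 0.983 | 0.958 | 0.986 |

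How often the route and the verdict vary:

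| Errors | Shift (mm) | Sent to rank-sum | t and rank-sum disagree | The three disagree |
|---|---|---|---|---|
| Normal | 0 | 0.104 | 0.015 | 0.029 |
| Normal | 12 | 0.092 | 0.061 | 0.111 |
| Normal | 19 | 0.097 | 0.039 | 0.069 |
| Skewed | 0 | 0.943 | 0.027 | 0.047 |
| Skewed | 12 | 0.966 | 0.151 | 0.189 |
| Skewed | 19 | 0.969 | 0.036 | 0.042 |

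Monte Carlo standard error near 0.05 is √(0.05 × 0.95 / 8000) = 0.0024.

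**3. Read the results.** Under no effect the gate-selected test rejects in about 0.050 of trials, so the two-stage rule does not inflate type I error here. Taking the best of three gives 0.063 (normal) or 0.076 (skewed). A second null simulation (6,000 trials per setting, baseline correlation 0.3 and 0.5) gave 0.065 and 0.063. The rank-sum branch is a live one: it is taken in about 10% of trials with normal errors and about 95% with skewed ones. The three analyses split on significance in 11–19% of trials at a 12 mm shift and in 4–7% at 19 mm.

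**The case against.** The strongest defence has four parts.

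*The order of the text implies a hierarchy.* The primary-outcome paragraph assigns the t or rank-sum test first, and the mixed model is introduced as an addition. That is a fair reading, and it weakens the case that the model competes for primary status. It does not remove the choice between t and rank-sum, and no explicit label is given.

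*A mean difference is still available.* A reader might infer that the plan has no mean difference with a confidence interval once normality is rejected. The documents do not support that. Continuous variables may be summarized by means with 95% confidence intervals, and the mixed model is planned whatever the gate says. What is missing is the decisive status of such an estimate.

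*Ranks can be combined after imputation.* A reader might infer that the rank-sum result cannot be pooled. That is too strong. A Mann–Whitney probability with its standard error, or a Hodges–Lehmann shift, can be pooled with extra work, and the latter is in millimetres under a location shift. The plan names neither, and the gate's own ambiguity across imputed datasets remains.

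*Such detail belongs in the analysis plan.* Omitted detail would. Here the protocol states a data-dependent rule: an analysis plan that follows it inherits the gate, and one that names a single test departs from it.

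A reader might also take log-transformation as a third route for the primary test, and one that is undefined for zero or negative changes. The text limits its scope: "For the descriptive analysis, data will be evaluated for normality and log-transformed when necessary". The primary-outcome paragraph offers only the t and Wilcoxon tests, and these and the mixed model are all defined for change scores.

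**Conclusion.** The point holds as a matter of what is estimated and which result decides. The endpoint and sample size are about a difference in means, but the stated rule lets the data replace that comparison with one of ranks, and a further model on the same contrast has no stated standing.

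It should not be read as a claim that the plan's testing rule is anticonservative. The two-stage rule held its level at about 0.050. The inflation to 0.063–0.076 needs someone to pick the most favourable of three results, which the protocol does not propose. At the planned 19 mm effect the three analyses mostly agree; disagreement is commoner at smaller effects.

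All simulated figures rest on the assumed distributions, on Shapiro-Wilk as the unnamed normality test, and on a baseline-adjusted model in place of the mixed model. They illustrate size and do not predict this trial. The contradiction between a mean-based endpoint and a possibly rank-based test rests on the text alone. The wording should be corrected before analysis; the trial's size and conduct are not in question.

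**What to change.** In Statistical methods and analysis:

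1. Name one primary analysis, whatever any normality test shows: the between-group difference in mean week-4 first-step VAS, adjusted for baseline VAS, with its 95% confidence interval. With baseline as a covariate, modelling week-4 VAS or change from baseline gives the same group difference, so the endpoint as defined is kept.
2. Say whether it is fitted as a linear model under multiple imputation or as a likelihood-based mixed model. Either gives an estimate and a standard error.
3. Drop the normality gate for the outcome tests.
4. Label the rank-sum test as a sensitivity analysis that cannot replace the primary result, and give any remaining model the same explicit status.

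Cost: wording only. Baseline VAS is already collected, and 40 per group stands.

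A plain t test on change would also be valid and would match the sizing. Baseline adjustment is the recommended choice, but fixing a single analysis in advance matters more than which mean-based one is chosen.
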